### Data Collection, Completeness, and Quality

The trial is based on pseudonymized routine data provided by the Zi. The dataset is based on aggregated practice data. Information collected includes: age groups and sex of patients, ARTI diagnoses (grouped and individual diagnoses), antibiotic prescriptions, group affiliation of the physician (intervention vs control), region, level of urbanization, and type of medical insurance of the patient.

### Statistical Methods

Data analyses will be performed in accordance with the STROBE statement [17]. For descriptive statistics, we will report the primary and the secondary outcome for the whole sample and by treatment allocation. Sampling units are practices. This evaluation is designed to confirm the two-sided primary hypothesis that the physicians’ antibiotic prescription rate after T1, regardless of the diagnosis, is lower in the intervention group than in control group 1. For investigating the primary outcome, we will use a negative binomial regression with the absolute number of annual antibiotic prescriptions as the dependent variable, the number of patients as the offset variable, and the antibiotic prescription rate before the introduction of RESIST as a covariate. To avoid bias, we will include region, specialization of the physician, proportion of male patients, proportion of different age classes (≤7 years, 8 to 18 years, 19 to 65 years, >66 years), proportion of insurance status (member, pensioner, noncontributory dependents), and the interaction between the proportion of male patients and region as additional covariates. The comparison between the intervention group and control group 1 is considered in a confirmatory manner. The comparison between the intervention group and control group 2 is additionally examined as a sensitivity analysis. The model for the secondary outcomes will be formulated in the same manner. The results will be represented as incident rate ratios with their 95% CIs and *P* values. Statistical analyses will be carried out with SAS, version 9.4 or the newer version (SAS Institute, Cary, NC, USA).

With respect to quality indicators (according to ESAC), sampling units are practices. The analysis will be carried out in the same way as the analysis of the primary and secondary outcomes considering the requirements of each indicator.

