## Methods

### Study Design

As RESIST is primarily a real-world project aiming to address as many participants as funding allows, it is evaluated in the form of a nonrandomized controlled trial. Patient and physician data are retrieved from routine health care data used by the Central Research Institute of Ambulatory Health Care in Germany (Zi). The Zi continuously analyzes prescription and diagnoses data on behalf of all German regional Associations of Statutory Health Insurance Physicians. The data analyzed include information on diagnosis as coded in practices and prescriptions as collected in pharmacies. Physicians not participating in the program serve as controls, either among the 8 statewide participating Associations of Statutory Health Insurance Physicians (control group 1) or among the federal states not eligible for participation in RESIST (control group 2). Antibiotic prescription rates before the intervention (T0: 2016, 1^st^ and 2^nd^ quarters of 2017) and after the intervention (T1: 3^rd^ quarter of 2017 until 1^st^ quarter of 2019) are compared.

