### Recruitment

Recruitment of participating physicians is undertaken in 8 German federal states and regions (Bavaria, Baden-Wuerttemberg, Lower Saxony, North Rhine, Westphalia-Lippe, Brandenburg, Mecklenburg-Western Pomerania, and Saarland), assisted by the respective regional Association of Statutory Health Insurance Physicians. General practitioners, primary care pediatricians, and practice-based otorhinolaryngologists can enroll in the RESIST program on a voluntary “first-come, first-served” basis. The maximum number of participating physicians per region is related to the size of the regional association. In total, we aim to include up to 3000 physicians in the program.

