### Control Group

Physicians not participating in the program serve as controls, either among the 8 participating regional Associations of Statutory Health Insurance Physicians (control group 1) or among the remaining associations not participating in RESIST (control group 2).

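### Control-group-2 comparison: group is determined by region, so the stated model cannot estimate the effect, and dropping region would leave the standard error too small if regional trends differ

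*Protocol article*

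**What the plan says.** All references are to the Protocol article.

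- **Where intervention practices are.** Recruitment: "Recruitment of participating physicians is undertaken in 8 German federal states and regions". Within those regions physicians "can enroll in the RESIST program on a voluntary “first-come, first-served” basis".
- **Where control group 2 is.** Study Design: "among the federal states not eligible for participation in RESIST (control group 2"). Control Group: "among the remaining associations not participating in RESIST (control group 2").
- **Model.** Statistical Methods: "Sampling units are practices", and "we will use a negative binomial regression with the absolute number of annual antibiotic prescriptions as the dependent variable". The number of patients is the offset, and the model has "the antibiotic prescription rate before the introduction of RESIST as a covariate". Region and the interaction of region with the proportion of male patients are further covariates. Results are to be given as rate ratios with 95% CIs and P values.
- **Status.** The comparison with control group 1 is confirmatory. For the other: "The comparison between the intervention group and control group 2 is additionally examined as a sensitivity analysis". No different model is given for it.
- **Clustering.** Sample Size allows only for patients within practices (ICC 8%, 160 patients per practice, design effect 13.72).

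**The concern.** In the comparison with control group 2, no region contains both groups, so the contrast lies entirely between regions. The model as described adjusts for region, and that adjustment removes the very contrast the analysis is meant to estimate. To get any estimate, the analyst must change how region enters.

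The easiest change is to drop region, and this creates a second fault. Practices in one region share infection waves, local programmes and prescribing trends. Adjusting for the T0 rate removes differences in level but not differences in trend. A model with practices as its only units would then treat thousands of practices as independent evidence on an exposure that varies over about 16 regions.

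The Discussion relies on controls from both participating and non-participating regions to deal with self-selection. The control-group-2 result is therefore part of the defence of a nonrandomized finding. It should not be arbitrary, and it should not have a hidden excess of false positives.

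**Working it through.** **1. The plan's own figure.** For 33.8% v 32.8%, two-sided 5% and 80% power, the usual two-proportion formula gives 34,866 per group (stated: 34,865). The design effect is 1 + 159 × 0.08 = 13.72. Then 34,865 × 13.72 = 478,348, and 478,348 / 160 = 2989.7, which rounds up to 2990 practices or 478,400 patients. The calculation reproduces. It concerns control group 1 and contains no between-region component.

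**2. Can the effect be estimated as written?** Take 16 regions (from the stated 8 out of 16), 8 per group.

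| Model | Columns | Rank |
|---|---|---|
| Control group 2: intercept, 15 region terms, group | 17 | 16 |
| The same plus proportion male and male-by-region terms | 33 | 32 |
| All three groups in one model with region | 18 | 17 |
| Control group 1: 8 regions, both groups in each | 9 | 9 |

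In every model that includes control group 2, one column is redundant. Software would drop a term or return a contrast that depends on which region parameter is set to zero. The control-group-1 model has full rank.

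**3. What happens if region is dropped?** The documents do not say that it will be; this is a conditional calculation.

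Inputs:
- Intervention: 2460 (Results; physicians, taken here as practices).
- Control group 2: N2 = 2460 to 10,000 (assumed).
- Residual practice variance v on the log scale, upper value: 0.1755. This is ICC × (1 − p)/p = 0.08 × 0.662/0.338 = 0.157, plus a Poisson part 1/(160 × 0.338) = 1/54 = 0.0185. It assumes no gain from T0 adjustment.
- Lower value of v: 0.065, an assumption for a gain from T0 adjustment.
- Regional SD s of the T0-to-T1 log change: not in the documents; assumed 0 to 3%.
- 8 v 8 regions of equal weight (assumed).

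Formulas:
- Model SE = √(v/2460 + v/N2)
- True SE = √(model SE² + s²(1/8 + 1/8))
- Type I error = 2[1 − Φ(1.96 × model SE / true SE)]

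Example with v = 0.065, N2 = 2460, s = 0.02: model SE = 0.00727; true SE = √(0.00727² + 0.01²) = 0.01236; ratio 1.70; type I error 24.9%.

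| s | v = 0.065, N2 = 2460 | v = 0.065, N2 = 10,000 | v = 0.1755, N2 = 2460 | v = 0.1755, N2 = 10,000 |
|---|---|---|---|---|
| 0 | 5.0% | 5.0% | 5.0% | 5.0% |
| 0.5% | 6.4% | 7.2% | 5.5% | 5.8% |
| 1% | 10.6% | 13.9% | 7.1% | 8.3% |
| 2% | 24.9% | 32.9% | 13.3% | 17.9% |
| 3% | 39.3% | 48.4% | 22.2% | 29.7% |

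For scale, the planned effect is ln(0.328/0.338) = −0.030.

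**4. Simulation check.** Null data were simulated for 8 v 8 regions with 300 practices each and dispersion 0.08, and a negative binomial model without region was fitted (400 runs per setting). Rejection rates were 4.3%, 10.5%, 18.5% and 47.8% for regional SDs of 0, 0.01, 0.02 and 0.05. For these settings the formula gives 5%, 8.6%, 18.8% and 50.4%, which agrees within simulation error.

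**The case against.** A reader might infer that the plan's control-group-2 interval is simply too narrow. The document does not support that. Region is in the stated model, and with fixed region terms there is no valid group estimate, hence no interval to be narrow. The narrow interval belongs to one possible repair that the article nowhere announces.

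It can also be said that a condensed article may leave random effects and variance estimators for a sensitivity analysis to a fuller plan, and that the statement on sampling units is general. That is a fair limit: the absence of a region error term would not on its own be a finding. What remains is that the article positively names region as a covariate, gives no other model for this comparison and promises CIs and P values. Followed as written, it yields no valid result.

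The size is open to challenge too. The regional SD and the variance of 0.065 are assumptions. The upper variance, derived from the document's ICC, gives the smaller inflation. Participant numbers depend on the size of the regional association, so the regions are not equal in weight. The 2460 are physicians, not practices. With a regional SD of zero nothing is inflated. All of this stands, so the percentages are illustrations.

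Finally, intervention physicians are volunteers, whereas control-group-2 physicians had no chance to enrol. If regional trends differ, part of the problem is bias, which a wider interval does not remove. This stands as well, and it is a reason against presenting a region-level test as isolating the effect of RESIST.

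**Conclusion.** The point holds in two linked parts. First, as described, the control-group-2 comparison cannot be estimated, because group is a function of region and region is in the model. This follows from the text and needs no assumption about variance. Second, if the repair is to drop region and keep practices as the only units, the CI is too narrow and the P value too small whenever regional trends differ. The excess is slight at a regional SD of 0.5% (type I error 5.5–7%), appreciable at 1% (7–14%) and large at 2–3% (13–33% and 22–48%). These figures rest on 8 v 8 equally weighted regions, 2460 physicians taken as practices, 2460 to 10,000 control-group-2 practices, and a residual variance of 0.065 to 0.1755.

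It would be wrong to extend this to the primary result. The confirmatory comparison with control group 1 lies within the same 8 regions, is identified with region as a covariate, and does not depend on this analysis. The point should be dealt with, but it concerns one sensitivity analysis.

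**What to change.** State a separate model for the control-group-2 comparison only. Either:

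- replace the fixed region terms, including the male-by-region interaction, with a random region effect and use small-sample degrees of freedom; or
- estimate the adjusted T0-to-T1 change in each region and compare the two sets of regions with a t test on about 14 df.

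Report the CI from that analysis in place of the practice-level one. Say in the text that this widens the interval to reflect variation between regions but does not remove confounding by region or by volunteering. Leave the control-group-1 model as it is.

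The cost is some wording, one different model and a wider CI for one sensitivity analysis. Even with no regional variation, the 14-df critical value of 2.145 instead of 1.96 makes the interval about 9% wider.

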### Sample Size

With respect to the primary outcome, a reduction of the physicians’ overall antibiotic prescription rate by 1% is assumed for RESIST (from 33.8% in the control group 1 to 32.8% in the intervention group). Without consideration of cluster effects, 2 × 34,865 patients are needed to show this effect with a power of 80% and a type I error of 5% (two-sided). Assuming an intracluster correlation (ICC) of 8% [16] and an average cluster size of 160 patients per practice, a design effect of 13.72 is determined. Overall, the sample size increases to 2 × 478,400 patients (956,800 patients in total). Thus, 2 × 2990 practices (5980 in total) are needed for the evaluation.

For the secondary outcome, a reduction of 3% in the physicians’ antibiotic prescription rate for ARTI is expected (from 30.5% in the control group 1 to 27.5% in the intervention group). Assuming a power of 80% and a type I error of 5% (two-sided), 2 × 3590 patients are required. With an ICC of 8% [16] and an average cluster size of 127 patients (diagnosed with ARTI) per practice, the sample size increases to 2 × 39,751 patients (79,502 patients in total). Hence, 2 × 313 practices are needed (626 practices in total). The sample size necessary to investigate the effect of the intervention on the primary outcome will be adequate to investigate its effect on the secondary outcome as well.

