## Discussion

With up to 3000 physicians participating in the program, RESIST is among the largest real-world interventions aiming at reducing inadequate antibiotic prescribing for ARTI in primary care. Long-term follow up of up to 21 months will allow for investigating the sustainability of the intervention.

As RESIST utilizes an open-label nonrandomized evaluation concept, potential bias has to be carefully addressed. Bias may arise from the fact that physicians most interested in reducing inadequate antibiotic prescriptions are also likely to be those most motivated to take part in RESIST. To counteract this, we make use of an attractive incentivization and reimbursement scheme. In addition, the inclusion of comparable practices not participating in the program (both among participating regions and among those not participating in RESIST) allows for control of this potential source of bias.

We will also minimize bias due to changed coding. For example, a clinically identical patient treated with antibiotics might be coded with lower respiratory tract infection initially but with pneumonia after the intervention, leading to an overestimation of the interventional effect. By measuring the overall antibiotic prescribing rate of antibiotics without regard to any specific disease as the primary outcome measure, we can exclude bias due to coding phenomena.

Last but not least, the RESIST program joins the ranks of other current initiatives to reduce inadequate antibiotic prescribing. Thus, contamination effects between the projects are possible. However, by including a high number of physicians and practices among half of all German states, we believe to be able to address this potential source of bias adequately.

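### Adjusting for one pre-RESIST prescription rate cannot separate a training effect from a trend that self-selected physicians already had, and the Discussion's assurance that the controls handle self-selection is not supported

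*Protocol article*

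**What the plan says.** All places are in the protocol article.

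- **Recruitment and Participants:** physicians enrol voluntarily, and those who complete the course are compared with physicians who did not take part.
- **Study Design:** T0 covers 2016 and the first half of 2017 (six quarters). T1 runs from the third quarter of 2017 to the first quarter of 2019 (seven quarters).
- **Statistical Methods:** the confirmatory contrast is intervention against control group 1. It uses a negative binomial model with a patient offset and "the antibiotic prescription rate before the introduction of RESIST as a covariate", together with region, specialty, sex, age classes, insurance status and a sex-by-region interaction. Control group 2 serves as a sensitivity comparison. No group-by-time term and no pre-trend check is mentioned.
- **Discussion:** it grants that "physicians most interested in reducing inadequate antibiotic prescriptions are also likely to be those most motivated to take part in RESIST". It then relies on incentives and on the inclusion of comparable non-participating practices, which it says "allows for control of this potential source of bias".
- **Sample Size:** the assumed effect is a change "from 33.8% in the control group 1 to 32.8% in the intervention group".

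**The concern.** In a non-randomised comparison of volunteers with non-volunteers, covariate adjustment is the main protection against confounding. Here it rests on the level of prescribing before RESIST and on the make-up of the practice. Neither measures the direction in which a practice was already moving. Physicians who want to prescribe fewer antibiotics may have been cutting back before they enrolled. A single pre-period rate is blind to that, and the model would credit the continued fall to the training.

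A stable difference in level is a lesser problem. The T0 rate is an imperfect measure of what a practice would have done in T1, so conditioning on it may remove only part of the difference.

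The planned effect is small, about 3% in relative terms, and the study is large. A modest bias could therefore come out as a significant confirmatory result.

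**Working it through.** **1. The plan's own figures.** Two proportions, 33.8% and 32.8%, with 80% power and two-sided 5%, give 34,866 per group (plan: 34,865). The plan states "an average cluster size of 160 patients per practice, a design effect of 13.72 is determined", and 1 + 159 × 0.08 = 13.72 agrees. Then 34,865 × 13.72 = 478,348, and 478,348/160 = 2,989.7, rounded up to 2,990 practices per group (2,990 × 160 = 478,400). The sample size is correct on its own inputs. The target rate ratio is 32.8/33.8 = 0.970.

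**2. Distance between the windows.** T0 spans 2016.0 to 2017.5 (midpoint 2016.75). T1 spans 2017.5 to 2019.25 (midpoint 2018.375). The difference is 1.625 years.

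**3. Differential trend that reproduces the target.**
- Relative: ln(0.328/0.338)/1.625 = −0.0300/1.625 = −0.0185, or about 1.8% per year.
- Absolute: 1 point/1.625 years = about 0.6 points per year.

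**4. Range of assumed differential trends, no training effect.** The ratio is (33.8 − 1.625 × trend)/33.8, from group means by quarter.

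| Extra fall, points per year | Ratio from averaged T0 and T1 | Ratio with group-specific T0 trend |
|---|---|---|
| 0.25 | 0.988 | 1.000 |
| 0.5 | 0.976 | 1.000 |
| 1.0 | 0.952 | 0.999 |

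The middle column is also what a simple group-by-period contrast returns, so that contrast alone does not remove a trend.

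As a check on the planned type of model, it was simulated with no training effect: 2,990 practices per group, 160 patients each, ICC 0.08, 40 runs, baseline rate as the only covariate. A relative drift of 1 point between T0 and T1 gave an IRR of 0.968, significant in every run.

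**5. Stable baseline gap, same simulation, no training effect.** With the stated ICC and cluster size, the reliability of an observed practice rate is 160 × 0.08/13.72 = 0.933.

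| Assumed situation | IRR from planned-type model |
|---|---|
| Participants 1, 3, 5 points lower | 0.996, 0.987, 0.976 |
| Same gaps, T0–T1 practice correlation 0.8 | 0.989, 0.971, 0.950 |
| Participants 3 points higher | 1.013 |
| Enrolment depends on the observed T0 rate (gap 3.3 points) | 1.003 |

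In the first row about 8%, 55% and 95% of runs were significant. With 40 runs these shares are rough: at 55% the standard error is √(0.55 × 0.45/40), about 8 percentage points. In the last row a simple group-by-period contrast gave 1.031. With stable gaps of 1 to 5 points that contrast gave 0.999 to 1.002.

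**6. The controls.** Control group 1 consists of physicians who could enrol and did not. Control group 2 had no chance to enrol, so it mixes would-be volunteers with others, but it is set against the same volunteers. Neither contrast separates volunteering from training.

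**The case against.** The strongest reply is that the plan does adjust. It uses the pre-period rate, specialty, region and patient mix, adds a second control group, and offers incentives meant to broaden enrolment beyond the already motivated. A full analysis plan may also hold a trend analysis that the article omits. This is fair, and the absence of a pre-trend check in the article is not in itself the point. Two things stand regardless: the confirmatory model as stated cannot do this job, and the Discussion makes a positive claim that the design described does not bear out.

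Three stronger readings are tempting, and the article does not support them.

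- A reader might infer that the baseline rate enters untransformed in a log-link model and that this is the main fault. The article does not give the scale. If it were untransformed, the scale alone would shift the IRR by only about 0.1% to 0.5% (0.999, 0.996, 0.995 with an error-free baseline and gaps of 1, 3 and 5 points).
- A reader might infer that the result must be biased in favour of the programme. The Discussion speaks of motivation, not of lower or falling rates. The sign reverses if participants start higher, and the bias nearly vanishes if enrolment depends on the observed T0 rate.
- A reader might infer that a group-by-period model should replace the primary analysis. It leaves a differential trend uncorrected and gave 1.031 under selection on the observed rate. The choice is between assumptions. The Results section also says that analysis began in February 2020, so changing the confirmatory model would carry its own cost.

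The simulations omit the other covariates, which might absorb some of the bias.

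**Conclusion.** The point holds in a conditional form. The planned adjustment cannot detect or remove a difference in trend that predates RESIST. A differential decline of about 1.8% per year, sustained over 1.625 years, is enough to yield the whole target IRR of 0.970 with no training effect. A stable baseline gap may leave further bias, whose size and sign depend on how physicians came to enrol. Every gap, trend and T0–T1 correlation used here is an assumption, because the article reports none. The Discussion's statement on control of self-selection is not supported by the two control groups described. None of this shows that the planned model is wrong as a primary analysis. It shows that a significant IRR near 0.97 could not, from that model alone, be told apart from self-selection.

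**What to change.** 1. Keep the planned baseline-adjusted model as the primary analysis.
2. Extract the practice data by quarter from the same source. Both windows split 2017 at mid-year, so data finer than annual totals must already exist; that they are available for each quarter is an assumption to confirm.
3. Estimate the group difference in trend over the six T0 quarters and report it with its confidence interval. A non-significant test does not show that the trends are parallel.
4. Prespecify a practice-by-quarter negative binomial sensitivity analysis with practice clustering, calendar-quarter effects and group × period, fitted without and with group-specific pre-trends. Since analysis is reported as started, date this addition and record what had been seen by then.
5. State that a causal conclusion requires the planned and trend-adjusted models to agree, and define agreement beforehand.
6. Reword the Discussion to say that self-selection is only partly addressed, and that the conclusion rests on the assumptions these analyses examine.

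The cost is finer extraction, more analysis, and wider intervals in the trend-adjusted model, because six quarters must support a projection over seven. The primary analysis and the sample size do not change.

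### The single stated model adjusts for region, but no region holds both intervention and control-group-2 practices, so the control-group-2 sensitivity comparison cannot be estimated as written

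*Protocol article*

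**What the plan says.** All places are in the Methods of the protocol article.

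- **Model (Statistical Methods).** The main analysis is given as: "we will use a negative binomial regression with the absolute number of annual antibiotic prescriptions as the dependent variable". Patient count serves as offset, and the pre-program prescription rate is a covariate. The adjustment set begins "To avoid bias, we will include region, specialization of the physician, proportion of male patients" and ends with "the interaction between the proportion of male patients and region as additional covariates".
- **Comparisons (Statistical Methods).** Intervention versus control group 1 is confirmatory. For the other control group the text says only: "The comparison between the intervention group and control group 2 is additionally examined as a sensitivity analysis". The secondary outcomes and the quality indicators are to be modelled in the same way as the primary outcome.
- **Location of the intervention group (Recruitment).** "Recruitment of participating physicians is undertaken in 8 German federal states and regions", which are then listed by name.
- **Location of control group 2.** Control Group: "among the remaining associations not participating in RESIST (control group 2"). Study Design: "or among the federal states not eligible for participation in RESIST (control group 2").
- **Location of control group 1 (Control Group).** The same 8 participating associations as the intervention group.

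**The concern.** A regression can separate a group effect from region effects only if at least one region contains both groups. Control group 1 meets this condition. Control group 2 cannot, because it is defined by lying outside the participating regions. If the stated model is applied to it, the group term is redundant once region is in.

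The failure can be silent. A package may drop one redundant column and still print an incidence rate ratio, interval and P value, which are the outputs the section promises. The Discussion cites comparison practices both inside and outside the participating regions as its means of controlling self-selection bias. A ratio produced by coding could then be read as supporting or contradicting the confirmatory result.

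**Working it through.** **The plan's own figures.** The only sizing stated for the primary outcome is against control group 1, and it reproduces.
- 33.8% versus 32.8%, two-sided 5%, 80% power: 34,866 per group (stated 34,865).
- Design effect: 1 + (160 − 1) × 0.08 = 13.72.
- 34,865 × 13.72 = 478,348 patients, and 478,348 / 160 = 2,989.7, rounded to 2,990 practices. 2,990 × 160 = 478,400, as stated.

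Nothing below depends on these figures.

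**Algebra.** Let D_r = 1 if a practice lies in region r, and G = 1 for the intervention group. Among intervention and control-group-2 practices, G = ΣD_r over the 8 participating regions, exactly and for every practice. With an intercept and region in the model, G adds no new direction.

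**Rank check on simulated practices.** The columns follow Statistical Methods: intercept (1), group (1), region (R − 1), region × proportion male (R − 1), proportion male (1), baseline rate (1), specialization (2), age shares (3), insurance shares (2). That gives 11 + 2(R − 1) columns. The article does not give the number of outside regions, so 8 and 9 were both tried (R = 16 and 17).

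| Comparison | Columns | Rank | Group effect estimable? |
|---|---|---|---|
| Intervention vs control 1, R = 8 | 25 | 25 | yes |
| Intervention vs control 2, R = 16 | 41 | 40 | no |
| Intervention vs control 2, R = 17 | 43 | 42 | no |
| Same, no interaction, R = 16 / 17 | 26 / 27 | 25 / 26 | no |
| All three groups, R = 16 / 17 | 42 / 44 | 41 / 43 | control 1 yes, control 2 no |
| Intervention vs control 2, no region terms | 11 | 11 | yes |

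**What a printed ratio would mean.** If the software drops one participating and one outside region as references, the printed ratio is the true ratio times exp(difference between those two regions' effects). Let the regions differ, after adjustment, with standard deviation s on the log scale (an assumption; the article gives no value). The difference between two regions then has standard deviation s√2. The planned effect as a ratio is 32.8 / 33.8 = 0.970. The central 95% of printed values, 0.970 × exp(±1.96 × s√2), is:

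- s = 0.02: 0.92 to 1.03
- s = 0.05: 0.84 to 1.11
- s = 0.10: 0.74 to 1.28

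Even the smallest of these is wider than the effect sought. In one simulated data set (true ratio 0.95, assumed s = 0.1, 8 + 9 regions, no interaction, proportion male and baseline rate as the other covariates), the printed ratio ran from 0.51 to 1.37 over the 8 × 9 = 72 choices of reference pair. Those are the extremes over all pairs, and the regional effects drawn were more spread than assumed, so this only illustrates the mechanism.

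**Does a pre/post model escape?** With one row per practice and period, the columns are intercept (1), region (R − 1), period (1) and group × period (1). For R = 16 that is 18 columns with rank 18, and group × period is estimable. Adding fixed region × period terms (R − 1 = 15 more) gives 33 columns with rank 32, and it is lost again. Regional trends must therefore enter as random variation.

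**The case against.** The best reply is that reuse of the model is inferred. The model follows directly on a hypothesis about control group 1, where it works. The control-group-2 sentence names no model, and the two statements about modelling in the same way concern secondary outcomes and quality indicators. An article may leave the form of a sensitivity analysis to an analysis plan that is not shown. This is fair as far as it goes, but the section offers one model and no alternative, and a reader who follows the text arrives at a fit that fails. That is an incompatibility between two stated elements, which is more than missing detail.

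A second reply is that region is called a covariate, without a statement that it is fixed, and its level is not defined. A random region effect, or a coarser variable that cuts across both sets of states, would restore estimability. That is correct, but neither is stated. Recruitment uses the term for the association areas, and on the federal-state wording in Study Design the two groups are equally disjoint.

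Three stronger readings are tempting and not supported:

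- *That control group 1 consists of physicians who declined, which would make control group 2 the only sound comparator.* Recruitment describes voluntary, first-come, first-served enrolment with a maximum per region, so non-participants may simply not have been reached or not have been in time. Intervention physicians are self-selected against either control group.
- *That the interaction makes the ratio refer to practices with 0% male patients.* The article does not say whether the proportion is centred.
- *That the trial's main result is at risk.* The control-group-1 model has full rank.

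**Conclusion.** The point holds for the control-group-2 sensitivity comparison. Under the stated model its rate ratio is not identified, whatever the sample size or the number of outside regions. The same applies to secondary outcomes and quality indicators if they are compared with control group 2 under this model.

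This rests on two readings of the text: that region means the association area or federal state and enters as ordinary covariate terms, and that the one stated model is the one to be used. The possible distortion of a printed ratio depends on between-region variation, which the article does not give, so the ranges above are conditional on assumed values.

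The defect should be fixed, but it does not threaten the trial. The confirmatory comparison with control group 1, its error rate and the sample size are untouched.

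**What to change.** State a separate model for control group 2, in one of two forms:

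- **(a) Post-period model without fixed region terms.** Remove region and region × proportion male. Keep the practice-level covariates and baseline rate, and add the level of urbanization, which the Data Collection section lists as collected. Include a region random effect, or use region-clustered standard errors with a small-sample correction.
- **(b) Pre/post model.** Use T0 and T1 as repeated outcomes with region main effects and group × period as the estimand. Allow for repeated measures within practice and for random variation between regions in time trends. Do not add fixed region × period terms. The baseline rate becomes an outcome and leaves the covariate list.

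In either case, state the limit. Under (a), differences between participating and non-participating regions remain confounded with the program effect. Under (b), the same is true of differing regional trends. The interval will reflect between-region variation. Say also whether the secondary outcomes and quality indicators are compared with control group 2 and, if so, under the same separate model.

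The cost is a paragraph of analysis-plan wording and a few lines of SAS. No new data are needed, since both periods and the urbanization field are already in the planned data set. Because the article reports that analysis began in February 2020, the choice should be dated and labelled as a clarification, with a statement of whether control-group-2 results had already been seen.
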